#### Exploratory outcomes

We will explore the impact of low-calorie days on dietary intake on the remaining normal eating days of the week from the 7-day food record. Physical activity on low-calorie days and normal eating days from the 7 days using an ACTi graph activity monitor. Also, any differences in adherence to the low-calorie day across the menstrual cycle.

### Trial follow-up

Participant flow through the trial is demonstrated in figure 1.

**Figure 1 F1:**
[figure not shown]
Study flow of participants through the Prevent 6:1 Trial. *A pregnancy test is not required if the participant meets the NICE criteria, that is, has not had sexual intercourse since the start of last normal menses or has been correctly and consistently using a reliable method of contraception. AUDIT, Alcohol Use Disorders Identification Test; BES, Binge Eating Scale30; GAD-7, General Anxiety Disorder-7; IPAQ, International Physical Activity Questionnaire; PHQ-9, Patient Health Questionnaire-9; PSQI, Pittsburgh Sleep Quality Index; NICE, National Institute of Clincial Excellence.

### Measurements

The full schedule of assessments is described in table 2.

**Table 2 T2:** Schedule of assessments for participants in the Prevent 6:1 Trial

Procedures	Screening/baseline	Week 0	Week 4 (±7 days)	Week 8 (±7 days)	Week 12 (±7 days)	Week 16 (±7 days)
Informed consent	x					
Screening questionnaires GAD (anxiety), PHQ (depression), AUDIT (alcohol dependence)	x					
BES (Binge Eating Scale)	x			x		X
Pregnancy test where required*	x					
Medical history	x					
PAR-Q readiness to exercise questionnaire	x					
Demographic/dieting history questionnaire	x			Update any changes		Update any changes
Assessment of menstrual cycle dates across the trial			x	x	x	x
Adherence to the low-calorie day each week across the trial			x	x	x	x
Body weight, body fat and lean body mass (bioelectrical impedance), waist/hip circumference	x					x
Mediterranean diet questionnaire	x			x		x
7-day food diary on Myfood 24 or paper diary	Completed week after baseline visit			x		Complete in week before week 16 visit
Alcohol intake (7-day recall), smoking and vaping questionnaire	x			x		x
Wear ACTigraph physical activity monitor for 7 days	Complete in week after baseline visit					Complete in week before week 16 visit
IPAQ short form (physical activity)	x			x		x
PSQI (sleep quality)	x			x		x
Intervention evaluation questionnaire and self-reported acceptability data						x
Baseline and exit face-to-face diet and physical activity advice		x				x
Dietitian review phone or video call/email			Offered dietetic support via phone or video call (MS teams) or email reviews at weeks 1, 4, 8, 12			
Assessment of dietitian time spent delivering the intervention			x	x	x	x
Assessment of engagement with dietitian calls/emails/online sessions and private Facebook group			x	x	x	x
Recording potentially diet related adverse events in the previous 4 weeks	x		x	x	x	x
Home weight recording and reporting to dietitian			x	x	x	
Optional anonymous NIHR demographic questionnaire	x					

* Pregnancy test is not required if the participant meets NICE criteria for excluding pregnancy (negative predictive value of 99%–100%) (https://cks.nice.org.UnitedKingdom/topics/contraception-assessment/management/assessment-for-contraception/): Is within the first 5 days of the onset of a normal (natural) menstrual period. Has not had sexual intercourse since the start of last normal menses. Has been correctly and consistently using a reliable method of contraception.

AUDIT, Alcohol Use Disorders Identification Test; GAD-7, General Anxiety Disorder-7; IPAQ, International Physical Activity Questionnaire; NICE, National Institute of Clinical Excellence ; NIHR, National Institute of Health Research; PAR-Q, Physical Activity Readiness questionnaire; PHQ-9, Patient Health Questionnaire-9; PSQI, Pittsburgh Sleep Quality Index.

### Physical measurements

Body weight, body fat and fat-free mass will be assessed using bioelectrical impedance Tanita MC980. Participants will be asked to avoid food and drink for 90 min prior to this measurement.^34^ Waist and hip circumferences will be assessed using standardised methods.^35^

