## Introduction

 Adult weight gain is a potentially modifiable risk factor for developing breast cancer as well as nine other weight-related cancers in women.^1^ In the UK, 35% of women are a healthy weight with 62% overweight or obese.^2^ On average, women in the UK gain 10 kg of weight during adult life, mostly between the age of 18 and 40 years.^3^ This level of weight gain increases weight-related cancers in women by 20%, specifically increased rates of breast (15%), endometrium (50%) and kidney cancer (30%).^1^

Weight gain is a consequence of habitual chronic positive energy balance, largely driven by excess energy intake and often high fat, high sugar diets.^3^ Once weight is gained, it is difficult to lose and keep off for both physiological and behavioural reasons.^4^ Weight gain is common among women attending family history clinics (FHCs) who are at increased genetic risk of breast cancer. Weight gain has an equal or greater effect on the relative risk for breast cancer among women with a family history of breast cancer compared with those without a family history.^5^ Thus, there is an unmet need for effective diet and physical activity interventions to prevent weight gain and manage breast cancer risk in this population.

Our previous research has demonstrated that the 5:2 diet, involving 2 days in the week with restricted energy intake (800–1000 kcal/day), is efficacious for weight loss in people with overweight or obesity,^6^ and this approach has been successfully implemented in many healthcare settings in the UK and worldwide including patients with cancer^7^ and type 2 diabetes.^8^ Our research has shown that intermittent diets (such as the 5:2 diet) can promote sustained awareness and mindfulness of diet choice and helps to control appetite, which in turn promote maintained lower energy intakes across the week.^9^ It is likely that the intensity of dietary restriction needed for the prevention of weight gain is less than that needed to induce weight loss. The present trial will therefore test whether a less intensive 6:1 intermittent diet including one low-calorie day/week is acceptable and has the potential to promote a healthy diet to prevent weight gain in women at increased risk of breast cancer who are a healthy weight.

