### Trial setting and recruitment

Participants will be identified from the regional FHC and the Cancer Genetics Clinics at Manchester University NHS Foundation Trust (MFT). Recruitment will be through direct invitation by members of the clinical teams, mailing the patient information sheet and promotion via the Prevent Breast Cancer charity website and related social media platforms such as Facebook and X. These women will have their attendance at the FHC and genetics clinics verified by a member of the relevant teams. The planned trial start and end dates are 17 March 2025 and 17 March 2026. All trial face-to-face assessments will be undertaken by the research team in a research facility at the main recruiting site at Wythenshawe Hospital. All participants will have a trial run-in week before they receive baseline diet advice when we ask them to record 7 days of habitual diet and wear an activity monitor to assess their habitual diet and physical activity patterns.

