### The 6.1 diet programme

#### Dietary advice

Participants will receive advice on adopting an intermittent 6:1 diet which involves one 1000 kcal day/week including ~70 g of protein and ~100 g carbohydrate. The 1000 kcal diet comprises 6–7 portions ~210 g of lean protein containing foods, 3–4 portions of wholegrain carbohydrates, one 7 g portion of fat, five 80 g portions of vegetables, two portions of fruit and three portions of dairy or dairy alternatives. An example of a low-calorie day is provided in table 1. The diet also includes 6 days/week of healthy eating Mediterranean-type diet which provides approximately 30% energy from fat (15% monounsaturated fatty acids, 8% polyunsaturated fatty acids, 7% saturated fatty acids), 25% energy from protein and 45% from low glycaemic load carbohydrate. The diet includes at least five portions of vegetables and two portions of fruit/day and is limited in alcohol (<10 units, 80 g /week) as described previously.^6^ Food and drink will be self-selected and not provided by the trial team. The diet can be successfully adapted for people of different ethnicities and those following omnivorous, vegetarian and vegan diets.

**Table 1 T1:** Example of a low calorie day for a mixed omnivorous diet which includes meat, fish or dairy

	Portion	Numbers of the food portions/day					
		Dairy	Protein	Carb	Veg	Fruit	Fat
*Breakfast*
Poached egg	1 egg	0	1	0	0	0	0
Grilled tomatoes	7 cherry tomatoes	0	0	0	1	0	0
Tea/coffee	1 mug	0	0	0	0	0	0
*Midmorning*							
Natural yoghurt ½ handful of berries	150 g 40 g	1	0	0	0	1/2	0
*Lunch*							
Wholegrain bread	1 medium slice	0	0	2	0	0	0
Tuna	⅓ of a 120 g can	0	1	0	0	0	0
Green salad	Cereal bowl (80 g) with oil-free dressing	0	0	0	1	0	0
Satsuma	1	0	0	0	0	1/2	0
*Mid afternoon*							
Low fat cheese	30 g /match box size	1	0	0	0	0	0
Apple slices	I medium apple (80 g)	0	0	0	0	1	0
Tea/coffee		0	0	0	0	0	0
*Evening*							
Vegetable rice	4 tablespoons cooked rice and 160 g of mixed vegetables	0	0	2	2	0	0
Chicken curry	90 g/average chicken breast (no skin) and ½ can tomatoes, 1 dessert spoon of oil	0	3	0	1	0	1
*Bedtime*							
Low fat houmous	1 level tablespoon	0	1	0	0	0	0
Pepper sticks	½ red pepper	0	0	0	1	0	0
Milk in drinks	1 small glass (200 mL)	1	0	0	0	0	0
Total portions a day		**3 portions**	**6 portions**	**4 portions**	**5 portions**	**2** **portions**	**1 portion**

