### Questionnaires

Participants will be asked to complete four paper questionnaires at the baseline visit to check eligibility; GAD-7,^23^ PHQ-9,^24^ BES,^22^ AUDIT.^38^ Eligible recruited participants will be asked to complete further questionnaires at baseline, weeks 8 and 16 (alcohol intake and smoking using 7-day recall,^30^ PSQI^32^ Mediterranean diet score,^29^ IPAQ^31^ using a secure web application (REDCap) (figure 1).^39^ A trial demographic questionnaire will also be requested at baseline. They will also be asked to complete an optional anonymous National Institute of Health Research (NIHR) demographic questionnaire. The NIHR is funding this project and they would like to understand whether research is reaching under-represented groups to help shape future research. Participants are informed their responses to questions are anonymous (not linked to their name or another identifier) and may be used for other educational and research purposes in the future.

Participants will also be asked to complete a trial specific diary over the 16-week programme, which records adherence to the low-calorie day of the 6:1 diet for each week and first day of each menstrual cycle while on the trial.

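### The week 16 weight and bioimpedance reading is not timed relative to the last low-calorie day, so a short-term, one-way fall may be counted as 16-week change

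*Protocol article*

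**What the plan says.** **Preparation.** Under Physical measurements, one device gives all three quantities: "Body weight, body fat and fat-free mass will be assessed using bioelectrical impedance Tanita MC980". The only condition stated is: "Participants will be asked to avoid food and drink for 90 min prior to this measurement".

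**Timing.** In Table 2 (Measurements), the row "Body weight, body fat and lean body mass (bioelectrical impedance), waist/hip circumference" is marked at screening/baseline and at week 16 only. The week 16 column carries a ±7-day window. Nothing there or under Physical measurements ties the visit to the diet day.

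**Order of events.** Trial setting and recruitment places the baseline visit ahead of the diet: "All participants will have a trial run-in week before they receive baseline diet advice when we ask them to record 7 days of habitual diet". The week 16 reading is taken while the participant is on the programme.

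**The diet day.** Dietary advice describes "one 1000 kcal day/week including ~70 g of protein and ~100 g carbohydrate". The article does not say which weekday it falls on or who fixes it.

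**Records that bear on timing.** The trial diary "records adherence to the low-calorie day of the 6:1 diet for each week and first day of each menstrual cycle"; whether the calendar date of the low-calorie day is entered is not stated. For the exit food diary and activity monitor, Table 2 says "Complete in week before week 16 visit".

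**The concern.** A day of restricted energy and carbohydrate can lower body weight for a short time through gut content, glycogen and the water stored with it. Bioimpedance infers fat-free mass from body water, so lost water can appear as lost lean tissue. A 90-minute abstention does not control for what was eaten the day before.

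Ordinary fluid variation affects both visits and mostly adds noise. The part caused by a programme low-calorie day can occur only at the exit visit, so it pushes in one direction. With a single arm, no comparison group carries the same artefact and allows it to be subtracted.

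Two readings are at stake. Change in weight is listed among possible benefits and would look better than it is. Fat-free mass matters because the Introduction names loss of lean mass as a possible detriment of reduced intake; here the artefact would look like harm. Both estimates could also be carried into planning of the efficacy trial.

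**Working it through.** The plan gives no figure for this effect, so there is none to reproduce. The steps below size it from the plan's own numbers plus one declared assumption.

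**Inputs**
- Adult weight gain: "On average, women in the UK gain 10 kg of weight during adult life, mostly between the age of 18 and 40 years" (Introduction).
- Planning adherence: 40% of weeks with a low-calorie day (Sample size). Full adherence (100%) is taken as the upper case.
- Days affected: the visit falls on the low-calorie day or the day after, so 2 of 7 days.
- Acute weight loss in an affected woman: 0.3–1.0 kg. This is an assumption; the documents give no value.
- Visit day unrelated to diet day, again an assumption.

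**Step 1: benchmark.** If the whole 10 kg is gained over the 22 years from 18 to 40:
- 10 / 22 = 0.455 kg per year
- 0.455 × 16/52 = 0.14 kg per 16 weeks

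This is an upper figure, because the article places most of the gain, not all of it, in that age range.

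**Step 2: share of women affected** = adherence × 2/7.
- 40% adherence: 0.40 × 2/7 = 11.4%
- Full adherence: 1.00 × 2/7 = 28.6%

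**Step 3: mean bias** = share affected × acute loss.

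| Adherence | Share affected | Loss 0.3 kg | Loss 1.0 kg |
|---|---|---|---|
| 40% | 11.4% | 0.03 kg | 0.11 kg |
| 100% | 28.6% | 0.09 kg | 0.29 kg |

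At 40% adherence the mean bias stays below 0.14 kg throughout. At full adherence it runs from 0.09/0.14 = 0.6 to 0.29/0.14 = 2.1 times the benchmark.

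**Step 4: when would the bias equal the benchmark?** Share needed = 0.14 / acute loss: 0.14/1.0 = 14% of women at the top of the range, 0.14/0.3 = 47% at the bottom. If every visit fell just after a low-calorie day, the bias would be the full 0.3–1.0 kg.

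**Step 5: comparison with random error.** The 90% CI half-width for a mean change is 1.645 × SD / √n. With an assumed SD of 1.5–3 kg (not in the documents):
- n = 30: 0.45–0.90 kg
- n = 15 (50% retention): 0.64–1.27 kg

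Under random visit timing, the mean bias is smaller than the half-width in every case shown. The interval does not reveal it, however, and it does not shrink as n grows.

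**The case against.** **Little depends on it.** The article says the trial is neither powered nor long enough to show weight change, the analysis is descriptive, and neither weight nor fat-free mass enters the progression criteria in Table 3. This stands and limits the weight of the point.

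**A condensed article may omit visit-booking detail.** A separate protocol exists, and the preparation rule cites a source. Silence here does not prove that a timing rule is missing there. Still, the article does state a preparation rule, and that rule leaves out the one condition specific to this intervention.

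**Part of the remedy is already collected.** The exit food diary covers the week before the visit, and Exploratory outcomes requires low-calorie days to be distinguished in it. For women who complete it, the last low-calorie day should be recoverable. This stands and makes the fix cheaper. Home weights at weeks 4, 8 and 12 also exist, but they are described as a safety check and give no fat-free mass.

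**The 40% may not suit this week.** It is a planning figure for the whole programme. The recorded week before the exit visit, among women still attending, may include a low-calorie day more often. Hence both adherence levels are shown. In the other direction, counting the visit day at full effect is generous, since an early visit precedes most of that day's restriction.

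**Stronger readings a reader might infer.**
- *The artefact exceeds the gain the diet is meant to prevent.* An affected woman's 0.3–1.0 kg is 2–7 times 0.14 kg, but that sets one person against a group mean. The mean bias does not exceed 0.14 kg at 40% adherence and does so at full adherence only in the upper part of the assumed range.
- *Women will place the day just before the weigh-in.* The article says food is self-selected; it does not say who picks the day, and nothing suggests clustering.
- *The run-in week shifts the exit reading to a later menstrual phase.* Baseline to exit is nominally 17 weeks, but ±7 days makes it 16–18 weeks, or 4.0–4.5 cycles of 28 days. There is no fixed shift, and contraceptive use means natural cycling cannot be assumed. At most this is noise.

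**Conclusion.** The point holds as a modest measurement weakness. The stated preparation does not control for a recent low-calorie day. The resulting error can arise at week 16 but not at baseline, and no control arm removes it. It is a possibility for women measured soon after such a day, not a certain loss in all participants.

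The mean bias of 0.03–0.29 kg across the two adherence levels rests on the assumed acute loss of 0.3–1.0 kg and on visit days being unrelated to diet days. That range concerns weight; the documents give no basis for sizing the effect on fat-free mass separately. The point matters most for an individual woman's fat-free mass reading and for any effect estimate taken forward to the efficacy trial. The decision to progress is not affected.

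**What to change.** 1. Within the existing ±7-day window, book the week 16 visit so that neither the visit day nor the day before is a low-calorie day. The visit is fitted around the diet; the diet is not altered.
2. Record the date of the last low-calorie day at that visit, or take it from the food diary for the preceding week. Because that diary may not cover the visit day itself, ask about it directly.
3. Report change in weight and fat-free mass for all women, and again without those measured within 48 hours of a low-calorie day (counted from the start of that day, which matches the booking rule).
4. If the full protocol already contains a timing rule, state it under Physical measurements.

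Cost: a booking instruction, one date on the case report form, one extra descriptive row for each outcome, and slightly less flexible scheduling. For visits already completed, step 3 should be possible from the food diaries where these were kept.

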### Assessment of dietary intake

Participants will be asked to record 7-day dietary records using the MyFood 24 app or a paper food diary for a week following their baseline appointment before starting the 6:1 diet programme, and at weeks 8 and 16 in the programme. Participants will receive support from the research dietitians and written information on setting up and completing the MyFood 24 diary.

### Assessment of physical activity

Physical activity will be assessed for 1 week following their baseline appointment and the week before their 16-week review using a wrist worn accelerometry monitor (ACTigraph GT9X). Participants will be asked to wear the monitor for as much of this period as possible. Monitoring days will be included if wear time is greater than 10 hours/day.^36^ Baseline and 4-month activity data will be included when it includes at least three valid monitoring days with at least one of those days being a weekend day. We will assess time spent in sedentary, light, moderate, vigorous activity and total time in moderate vigorous physical activity. Also step count and vector magnitude average counts to get a measure of overall activity.^37^ Data will be analysed using ACTi Life 6 Software.

### Questionnaires

Participants will be asked to complete four paper questionnaires at the baseline visit to check eligibility; GAD-7,^23^ PHQ-9,^24^ BES,^22^ AUDIT.^38^ Eligible recruited participants will be asked to complete further questionnaires at baseline, weeks 8 and 16 (alcohol intake and smoking using 7-day recall,^30^ PSQI^32^ Mediterranean diet score,^29^ IPAQ^31^ using a secure web application (REDCap) (figure 1).^39^ A trial demographic questionnaire will also be requested at baseline. They will also be asked to complete an optional anonymous National Institute of Health Research (NIHR) demographic questionnaire. The NIHR is funding this project and they would like to understand whether research is reaching under-represented groups to help shape future research. Participants are informed their responses to questions are anonymous (not linked to their name or another identifier) and may be used for other educational and research purposes in the future.

Participants will also be asked to complete a trial specific diary over the 16-week programme, which records adherence to the low-calorie day of the 6:1 diet for each week and first day of each menstrual cycle while on the trial.

### Data analysis plan

Descriptive and basic statistics will be reported (number, frequencies and percentages and median and IQR as appropriate) as well as the level of missing data. Descriptive data for energy and macronutrient intake and physical activity will be assessed on the low-calorie days and the remaining days of the week to explore if the 6:1 intermittent diet has a carryover effect across the week.

Adherence to the 6:1 intermittent diet across the weeks of the menstrual cycle will inform any effects that the menstrual cycle has on adherence.

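### The two sets of days named for the carryover question cannot show carryover without habitual intake; the run-in week should be named as the reference

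*Protocol article*

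**What the plan says.** The Data analysis plan section describes energy, macronutrients and activity on two sets of days, "low-calorie days and the remaining days of the week to explore if the 6:1 intermittent diet has a carryover effect". Exploratory outcomes frames the question in the same way. For diet, the trial will "explore the impact of low-calorie days on dietary intake on the remaining normal eating days of the week", using the 7-day food record. For activity it lists "Physical activity on low-calorie days and normal eating days from the 7 days using an ACTi graph activity monitor". Neither section names a reference period outside the diet week.

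Such a period is collected. Under Trial setting and recruitment, women in the run-in week "record 7 days of habitual diet and wear an activity monitor to assess their habitual diet and physical activity patterns", before any diet advice. Under Assessment of dietary intake, food records are kept "for a week following their baseline appointment before starting the 6:1 diet programme, and at weeks 8 and 16 in the programme". Activity is monitored in the run-in week and again in the week before the 16-week review. Activity data from a period are used if there are "at least three valid monitoring days with at least one of those days being a weekend day".

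**The concern.** The Introduction argues that intermittent diets help control appetite and so keep intake lower throughout the week. In that sense, carryover is a difference between the unrestricted days and what the woman would habitually eat. The two sets of days named in the analysis plan are the restricted day and the unrestricted days of the same week. The restricted day is low because the programme makes it low, so a large gap between the two is expected whether or not there is carryover. Carryover in the hoped-for direction makes the gap smaller, which invites misreading.

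At stake is whether a food record that participants keep for 7 days on three occasions can inform a question that is part of the diet's rationale. Among the listed outcomes, diet change is measured by the Mediterranean diet score, which Table 2 shows as a separate questionnaire. No listed outcome explicitly uses the run-in food record for energy intake.

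**Working it through.** The plan gives no figure for this analysis, so there is none to reproduce. The question is what the named quantities can identify.

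**Inputs**
- L = 1000 kcal, intake on the low-calorie day (Dietary advice), taken as achieved.
- H = habitual daily intake. The document does not give it; values from 1700 to 2200 kcal are assumed.
- c = carryover on the other six days, negative if intake falls and positive if the woman compensates.
- R = H + c, mean intake on the other six days.

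**Same-week gap**

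R − L = (H − 1000) + c. One observed gap contains two unknowns:

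| Assumed H | c | R = H + c | R − 1000 | R − H |
|---|---|---|---|---|
| 1800 | 0 | 1800 | 800 | 0 |
| 2000 | −200 | 1800 | 800 | −200 |
| 2200 | −400 | 1800 | 800 | −400 |
| 1700 | +100 | 1800 | 800 | +100 |

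The same 800 kcal fits no carryover, carryover of two sizes, and compensation. Neither the presence nor the direction of carryover can be read from it. Describing the two sets side by side without subtracting them does not help: that yields L and R, and R still cannot be split into H and c.

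**Holding H at 2000 kcal**
- c = −200: the gap is 800.
- c = 0: the gap is 1000.
- Full compensation, c = (2000 − 1000)/6 = +167: the gap is 1167.

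The gap is large and positive in all three cases. The change from run-in is −200, 0 and +167.

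**What the run-in difference contains**

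R − H equals c only if nothing else moves the other six days. In this single-arm trial those days also carry Mediterranean-type diet advice and activity advice, and recording habits and time may change as well. If a stands for the effect of that advice and t for recording and time, then R − H = c + a + t. H cancels, but a and t remain.

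**Why to match on weekday and weekend**

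Taking one day out of the diet week changes its mix. Weekend days are 2/7 = 29% of the run-in week. They are 2/6 = 33% of the remaining days if the low-calorie day is a weekday, and 1/6 = 17% if it is a weekend day.

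**Activity**

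The 1000 kcal term does not apply, because activity on the low-calorie day is not prescribed by energy. The same-week comparison therefore answers a real question: whether women move less on the low-calorie day. It needs that day to be a valid wear day, and three valid days including a weekend day can be met without it.

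**The case against.** The strongest reply is that the article says data will be assessed on both sets of days; it does not say that one is subtracted from the other. A comparison with run-in is not excluded, the run-in week exists to capture habitual patterns, change in objectively measured activity is already listed among the other outcomes, and a separate analysis plan is available on request. This stands as far as it goes: a reader might infer that the investigators will ignore the run-in data, and the article does not support that. But these two sets are the only ones tied to the carryover purpose, and they cannot serve it even when described separately. Naming the reference is a better method, not a missing detail.

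A reader might also infer that change from run-in would isolate carryover. It would not, for the reasons shown in the working.

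It is equally tempting to treat the same-week activity comparison as mistaken. It is not: the Introduction raises reduced activity with reduced calorie intake, and the comparison addresses that directly.

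The wear-time rule governs whether a period's activity data are used overall. Nothing says that a woman without a valid low-calorie day enters the day-type description, so the rule is not itself wrong; it only fails to guarantee what that comparison needs.

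Two further figures should not be leaned on.
- Multiplying 30 by 50% retention and 40% adherence gives 6 women with a low-calorie day in the week-16 record. Those percentages only illustrate interval width in the Sample size section. At the green thresholds of Table 3 (70% and 50%) the product is 30 × 0.7 × 0.5 = 10.5, and either product assumes that average adherence holds in the recorded week.
- The chance that the low-calorie day is among the valid days comes to 3/7 = 43% only if every woman has the bare minimum of three valid days and the low-calorie day is equally likely to fall on any day. The protocol asks for as much wear as possible.

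**Conclusion.** The point holds for intake: the two named sets of days cannot by themselves show whether carryover is present or in which direction. The algebra does not depend on the value of H. The 800 kcal illustration does rest on assumed habitual intakes and on the low-calorie day being eaten as prescribed. The run-in week is the best comparator available in this design, not a clean one. For activity, the same-week comparison is valid for its own question but does not measure carryover to other days.

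The severity is minor. The outcome is exploratory and descriptive, the article states that the trial is not powered for changes in diet or activity, and no progression criterion in Table 3 rests directly on this analysis. A reader might infer that the decision to go on to an efficacy trial is compromised; the document does not support that.

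**What to change.** Amend the Data analysis plan and Exploratory outcomes sections as follows.

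1. Add, as the main exploratory carryover summary, each woman's mean on non-restricted days at weeks 8 and 16 minus her run-in mean, matched for weekday and weekend. For activity, use week 16 only. Report the number of women contributing at each time point.
2. Label this as change from run-in on non-restricted days. State that in a single arm it also reflects the concurrent diet and activity advice, changes in recording, and time, and is not a causal carryover effect.
3. Keep the same-week comparison of activity as a separate question, whether activity is lower on the low-calorie day. Limit it to women with a recorded low-calorie day that is also a valid wear day.

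The cost is a few sentences. All the data are already planned, with no new visits or participants. The downside is that fewer women will contribute to the same-week activity comparison.
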